### Overview of the study

Advertisement of the trial will be made in social media, and all the patients with LBP presenting at the study site will be invited to participate. Interested candidates will be screened for eligibility. Eligible patients with non-specific LBP will then be enrolled in the trial and be randomly assigned to one of the two study groups. All the participants in the experimental group will receive pain education and those in the control group (CG) will receive guideline-based physiotherapy treatment. All the participants will be assessed at baseline and 1 week following treatment. Details describing the schedule of enrolment, interventions and assessment are presented in table 1, in the manner recommended by SPIRIT checklist.^32^

**Table 1 T1:** Schedule of enrolment, assessment and interventions

Timepoint	Study period				
	Enrolment	Allocation	Post allocation		Final Assessment
	−T_1_	T_0_	T_1_	T_2_	T_3_
Enrolment					
Eligibility screening	X				
Explain study procedure/provide participant information sheets	X				
Informed consent	X				
Random treatment allocation		X			
Intervention					
Experimental intervention (PEG)				X	
Control group (CG)				X	
Assessment					
Baseline descriptive variables					
Sociodemographic information (age, sex, address, occupation, religion and ethnicity)			X		
History					
Pain history (site of pain, duration of pain, continuous or intermittent pain, aggravating and relieving factors)			X		
Comorbidities			X		
Feasibility					
Willingness to participate in a randomised controlled trial	X				
Acceptability of random allocation to one of the two groups	X				
Acceptability of intervention session (one session in a week with home treatment programme throughout the week)	X				
Feasibility of blinding the assessor*					X
Eligibility and recruitment rates	X				
Acceptability of screening procedures*					W
Understanding possible contamination between the groups					X
Evaluating the credibility of the intervention			X		X
Adherence to intervention					X
Treatment satisfaction					X
Difficulty in understanding the treatments					X
Secondary outcomes					
PROMIS Pain interference			X		X
PROMIS Pain intensity			X		X
Quality of life			X		X
PROMIS Sleep disturbance			X		X
PROMIS Depression			X		X
GROC			–		X
PCS			X		X
CD-RISC-10			X		X

*Assessed by the therapist providing intervention; all other outcomes are assessed by the blinded outcome assessor.

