#### Home advice for PEG group

A printed handout of the pain education material will be provided only to the study participants in the PEG. Participants will be advised to read them, and perform physical activity including walking for approximately 30 min. Education accompanied by written information has been reported to yield the largest effects on fear component of emotional distress.^47^ However, education level of Nepalese is low (65%); 37 we will adapt the written materials to incorporate many more images than text.

For those who cannot read, the family member(s) will be encouraged to read out the materials to them. To complement the written materials, we will also provide an audio-recording of the pain education session to the patients as an online URL link to Nepali patient education material stored in the cloud or will be copied to their smart phones or both for those who have the facilities to use them. The pain education advice will be directed towards reducing brain’s perception of movement and exercise as a threat encouraging participants to slowly pace the movement, physical activity and exercise. This is thought to desensitise the sensitive nervous system and improve function. A written instruction to perform general exercises and physical activity will be sent to the participants. Participants will be discouraged to use a lumbar corset and rest as coping strategy, whereas physical activity and return to work will be encouraged. A reminder to perform home exercises will be sent to all participants for a total of 5 days in the week.

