### Outcome measures

The details of primary feasibility outcomes are presented in table 2.

**Table 2 T2:** How will each primary feasibility objective be assessed?

Serial Number	Objectives	Measures to assess specific objectives	Statistical analysis
1	Willingness to participate in a randomised controlled trial	All the consecutive participants presenting at the physiotherapy department will be approached and invited to participate. The number and rate of participants willing versus not willing to participate will be recorded, as well the reasons for not wanting to participate.	Total number of patients not willing to participate will be summed and reasons for non-participation collated.
2	Feasibility of blinding the assessor	Feasibility of blinding will be assessed by asking the assessor two questions at the end of the follow-up assessment: 1. Did you receive any information that indicated to you which group the participant was assigned to? 2. How did you receive information about group assignment? Assessor’s guess regarding group assignment group will be recorded for each participant. The responses will be coded as correct or incorrect guess.	The frequency and relative rates of ‘*Yes*’ and ‘*No*’ as the answer to the first question will be computed, as will the frequency and relative rates of correct and incorrect guesses. Finally, reasons for guesses will be recorded as verbatim and reported.
3	Eligibility and recruitment rates	The total number of participants screened, found eligible and recruited will be recorded during the screening and recruitment process. The reasons why the participants were ineligible for study inclusion will be recorded for every participant who did not meet eligibility criteria. Reasons for declining participation will be recorded for every eligible individual who declined participation. Consent rates will also be recorded.	The number of participants screened, who were eligible, who consented to participate, who refused to participate will be computed. The reasons for exclusion and refusal will also be collated.

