6	Understanding possible contamination between the groups	Contamination between the groups will be assessed by asking all the study participants the following questions at 1 week following treatment: *1. ‘Have you talked to other participants in this study about the intervention they are receiving?’; If yes, further ask, ‘Was your attitude towards the intervention, or intervention changed after talking to one of the participants in the other group?’;* *2. ‘Are you aware of the intervention that any participants in the other group are receiving in the study?’;* *3. Are any of the participants in the other group aware of the type of intervention you are receiving in this study?’* Participants in the control group will be asked the following question: ‘*Did you read the pain education booklet or watch the video which is one of the components of the intervention group*?’ These questions are adapted from a cotwin controlled feasibility trial.^62^	The frequencies of the participants who responded affirmatively to each question will be computed separately for each treatment condition.

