7	Credibility and acceptability of the interventions	Treatment credibility will be assessed using five questions adapted from Borkovec and Nau.^63^ The questions will be modified to fit ‘Pain education’ and ‘Control group’ as a treatment for patients with LBP and will be administered to all the participants in both conditions. One, important cultural adaptation for the scoring will be made by changing the numerical scale proposed by Borkovec and Nau to a Verbal Rating Scale, because Numerical Rating Scales have been shown to be unsuitable in Nepalese with musculoskeletal pain, especially in those who are older and have low educational attainment.^64^ Responses for each of the five questions will be recorded on a Likert scale where, 0=‘*Not at all*’, 1=‘*A little bit*’, 2=‘*Somewhat*’, 3=‘*Quite a bit*’, 4=‘*Very much*’. The questions are: 1. How logical does the treatment provided seem to you for the management of low back pain? 2. How confident would you be that this treatment would be successful in reducing pain? 3. How confident would you be in recommending this treatment to a friend or family who also has LBP? 4. If you were having low back pain again, would you be willing to undergo such treatment? 5. How successful do you feel this treatment would be in reducing pain in other parts of the body, for example, knee pain? All the questions will be asked at baseline and at 1 week following treatment.	Mean of the total scores on the credibility scale will be computed separately for each condition. Between-condition differences in creditability will be evaluated using a t-test.
8	Adherence to the intervention	Adherence to treatment will be assessed by asking the participants in both conditions to maintain a record of daily home treatment that was followed by every participant. The participants will tick mark a box for every day for a total of 5 days between the two assessment time-points to indicate their adherence to prescribed home exercise programme. Additionally, participants will be requested to record any deviation of prescribed home treatment programme (eg, additional visit to the clinic and use of other interventions). Finally, question regarding non-adherence will be asked.	The total number of treatment adherence days will be summed for each treatment condition separately. Deviation from the treatment protocol will be recorded. Finally, the reasons for non-adherence will also be listed.

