All but one secondary outcome measures have been shown to be reliable and valid in Nepali populations. The measure of quality of life (QOL) is not yet validated at the time of writing the protocol; however, we have included it as a secondary outcome measure, because assessment of QOL is a recommended measure by core outcome sets in clinical trials for LBP.^53^ We hypothesise that this measure is comprehensible and will show adequate validity in the Nepalese sample. We will evaluate the validity of the measure before using it in the full clinical trial.

A research assistant will interview all the study participants to make the study procedures consistent and to allow for the inclusion of participants with little or no education. The interviews will be administered by a physiotherapist who will be blind to group assignment. Secondary measures include the four PROMIS short-form measures assessing pain interference,^54^ pain intensity,^54^ sleep disturbance,^54^ and depression,^54^ as well as the 13-item Pain Catastrophizing Scale,^55^ Connor-Davidson Resilience Scale,^56^ Global Rating of Change^57 58^ and a QOL scale. All the items in each PROMIS measure will be summed to obtain raw scores for each scale. The raw scores of each measure will then be converted to T-scores, with a mean of 50 and SD of 10 and recorded (www.assessmentcenter.net). Details of the measures with their measurement properties are presented in table 3.

**Table 3 T3:** Secondary outcome measures

Domain	Name of outcome measure	No. of Items	Response scale	Scoring	Measurement properties of Nepali versions of the scale
Pain interference	PROMIS Pain Interference short-form 6b^54^	6	5-point, ordinal	Respondents are asked to rate how much pain interfered with their daily life (eg, enjoyment of life, ability to concentrate and day-to-day activities) in past 7 days on 5-point Likert scales (=‘*Not at all*’, 2=‘*A little bit*’, 3=‘*Somewhat*’, 4=‘*Quite a bit*’, 5=‘*Very much*’). Responses are scored as a T-score that can range from 0 to 100, with a mean of 50 and SD of 10 in the normative sample.	Good internal consistency (Cronbach’s alpha=0.85). Excellent reliability (ICC=0.80) in a sample of individuals with chronic pain from Nepal.^54^

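### The blinded assessor has to put a control-only question before the end-of-visit blinding check, so the interview form itself can trigger the >70% correct-guess criterion

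*Protocol article*

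**What the plan says.** - **Who asks.** In Table 1 (Overview of the study) only two feasibility items carry an asterisk: assessor blinding and acceptability of screening. The footnote reads "Assessed by the therapist providing intervention; all other outcomes are assessed by the blinded outcome assessor". Contamination has no asterisk and is scheduled at T3, so it falls to the blinded assessor.
- **How.** The Outcome measures section says "A research assistant will interview all the study participants to make the study procedures consistent" and "The interviews will be administered by a physiotherapist who will be blind to group assignment".
- **What is asked.** Table 2 item 6 puts several contamination questions to everyone at 1 week. It then adds one more, introduced by "Participants in the control group will be asked the following question", on whether the person read the pain education booklet or watched the video.
- **When blinding is checked.** Table 2 item 2: "Feasibility of blinding will be assessed by asking the assessor two questions at the end of the follow-up assessment". The same item says a guess of the arm is recorded for each participant and coded correct or incorrect. It gives the guess no separate time.
- **What depends on it.** Assessor blinding is one of the primary feasibility outcomes. Table 4 calls for a modified protocol if more than 70% of guesses are correct.
- **Materials supplied.** Home advice for PEG group describes a printed handout and adds "we will also provide an audio-recording of the pain education session to the patients". No video is described.

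**The concern.** An interviewer who does not know the arm cannot tell whom to ask a control-only question. Asking it marks the participant as a control, and leaving it out marks the participant as pain education. The three statements (blinded assessor collects contamination, one question for controls only, blinding checked at the end of that visit) cannot all be followed with the blind intact. Nothing in the article gives the question to someone else, masks it or places it after the guess.

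What is at stake is mainly the blinding result itself. The study exists to tell the sponsor whether a full trial can be run with these procedures. A correct-guess rate driven by the form does not answer that for blinding. The secondary outcomes are exposed too if they are asked after this question.

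A smaller, separate fault lies in the same question. It names a video where the plan supplies an audio recording, so a control who only heard the audio can truthfully answer no. With 20 controls each missed case is 1/20 = 5 percentage points among controls, and Table 4 separates 0%, below 15% and 15% or more.

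**Working it through.** The plan gives no figure to reproduce here, since the 40 participants are a team judgement and not a power calculation. The check asks how the disclosure acts on the plan's own 70% rule.

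**Inputs from the protocol**
- 40 participants, 20 per arm (Sample size).
- Modify if the correct-guess rate exceeds 70% (Table 4).
- Attrition bands at 15% and 30% (Table 4), used for sensitivity.

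**Assumptions (not in the protocol)**
- Where allocation is not disclosed, the assessor guesses at chance, p = 0.5.
- Under attrition the arms remain equal in size.

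**Threshold.** 0.70 × 40 = 28, so exceeding 70% needs at least 29 correct.

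**Upper bound: both arms disclosed.** Asking the question identifies 20 and omitting it identifies the other 20. The rate can reach 40/40 = 100%, and the rule is met by design.

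**Conservative case: only controls disclosed.** The assessor does not draw the inference from the question's absence.
- Expected rate = (20 + 0.5 × 20)/40 = 30/40 = 75%.
- The rule is met if at least 29 − 20 = 9 of the 20 chance guesses are right: P(Bin(20, 0.5) ≥ 9) = 0.748.

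**Intact blinding.** P(Bin(40, 0.5) ≥ 29) = 0.003.

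**With attrition**

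| Assessed | Correct needed | Intact blinding | Controls disclosed |
|---|---|---|---|
| 40 | 29 | 0.003 | 0.75 |
| 34 (15% lost) | 24 | 0.012 | 0.83 |
| 28 (30% lost) | 20 | 0.018 | 0.79 |

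The last column is P(Bin(20, 0.5) ≥ 9), P(Bin(17, 0.5) ≥ 7) and P(Bin(14, 0.5) ≥ 6).

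**How much disclosure is enough.** If a share q is disclosed, the expected rate is q + 0.5(1 − q). Setting this to 0.70 gives q = 0.20/0.50 = 0.40. Disclosure for 40% of participants already puts the expected rate at the threshold, and controls alone are 50%.

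**The case against.** Several points on the other side have force.

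- **The leak would be noticed.** Item 2 asks the assessor how information on allocation was received and records reasons verbatim. Table 4 then has the team improve blinding from that feedback, which is what a feasibility study is for. This stands in part: the form would probably be named as the source. But the study would have spent its one measurement of blinding on a known fault, and the repaired procedure would reach the full trial untested.
- **Item order is not stated.** A reader might infer that every follow-up outcome loses its blinding. The protocol does not support that. The control-only question is asked at T3, and if the secondary outcomes come before it, this question does not affect them. The article may also have left item order to the interview form. In addition, the global rating of change is the participant's own report and participants are not blinded, so assessor knowledge adds less bias there than it might seem.
- **The time of the guess is inferred.** Only the two blinding questions are explicitly placed at the end of follow-up. Reading the guess as taken then is natural but not stated.
- **Credibility items.** A reader might infer a second leak, as early as baseline, from "The questions will be modified to fit ‘Pain education’ and ‘Control group’ as a treatment for patients with LBP". But the five items printed in Table 2 item 7 form one set that names neither arm, given to participants in both conditions. Arm-specific forms are possible, not established.
- **The other contamination questions.** They ask about awareness and contact with other participants. That the answers would reveal the arm is speculation.
- **Consequences are limited.** No efficacy testing is planned, effect sizes do not decide progression, and blinding is one of several Table 4 criteria.

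None of this removes the control-only question or the conflict over who asks it.

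**Conclusion.** The plan is wrong as written on one point. The blinded assessor is given a question that can be asked correctly only by someone who knows the arm, at a visit that ends with the blinding check. The correct-guess rate can reach 100%. In the conservative case it is expected to be 75%, with a probability of about 0.75 of crossing the 70% line (0.75 to 0.83 over the attrition range), against 0.003 to 0.018 with intact blinding. These figures assume chance guessing where allocation is not disclosed, equal arms at follow-up, and a guess taken after the contamination questions.

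Harm to the secondary outcomes is conditional on an order that the protocol does not give. A credibility leak needs confirming, not correcting. The video wording is a separate inconsistency that bears on the contamination estimate and not on blinding.

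**What to change.** 1. **Fix the order at T3.** Collect the secondary outcomes first. Next take the assessor's written guess and the two blinding questions. Only then ask contamination and the other treatment-related items (credibility, adherence, satisfaction, difficulty). Amend Table 2 item 2 so that the blinding check precedes these items and does not close the visit.
2. **Reword the control-only question** to name what is actually supplied: the booklet or the audio recording.
3. **Confirm in item 7** that the single neutral credibility wording already printed is used in both arms, at baseline and at 1 week.

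Putting the booklet question to both arms is not enough by itself, because pain education participants would answer yes and so reveal their arm. Having someone other than the blinded assessor ask it would work, but needs a second person at the visit.

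Steps 1 to 3 cost a re-ordering and rewording of one interview form, with no extra staff, visit or participants. They should be made before the form is used at follow-up.

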### Pain education for LBP

Patient education for LBP that has been investigated in randomised controlled trials is basically of two types: biomedical education and pain biology education.^26^ The first refers to educating patients about vertebral anatomy and pathoanatomy of the spine, which has been shown to be ineffective and may even have negative effects on LBP outcomes.^26^ However, the second type of education—pain biology education (hereafter called as ‘pain education’)—has been shown to have positive effects on both pain and disability.^27 28^ Pain education is structured education programme with specific aims and objectives.^29^ This intervention has a list of target key concepts to be delivered and includes the curriculum contents to deliver the key concepts using up-to-date pain science knowledge, stories and metaphors.

It has been previously hypothesised that this type of education programme using metaphors and stories may be an effective intervention in Nepalese with chronic pain.^30^ However, the pain education materials that have been developed in western cultures are not necessarily valid and equally effective in reducing pain and disability in non-western cultures. Therefore, when developing pain education materials in a newer language or culture, (significant) cultural adaptations of the education materials may be required to make it suitable for the target population, as culturally inappropriate education may not produce desirable results.

Therefore, in order to evaluate the effectiveness of pain education in individuals with non-specific LBP from Nepal, culturally appropriate pain education materials should first be developed for Nepal, specifically. However, it is possible that the adaptations made could potentially reduce its effectiveness. Thus, before testing the adapted pain education in a full clinical trial, a feasibility study is needed in order to determine if a full clinical trial based on the adapted intervention is warranted, or if additional modifications may be needed prior to performing the full trial.

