#### Pain education group

The pain education will be delivered to the PEG only. We will use the pain education handouts in Nepali for Nepalese with LBP based on the resources developed by [name] and [name], called Explain Pain.^29 40 41^ It has evolved in over 15 years^42^ and undergone changes and advances.^29 40 41^
^43 44^ Pain education is delivered to provide reassurance, which means removal of fear and concerns about illness.^45^ Reassurance is among the core aspects of management of patients with non-specific problems such as LBP.^46^ Although there are no gold standard ways to provide reassurance and alleviate fear and concerns about a disease or its consequences, empathy and collaboration are thought to play important role.^47^ The Pain education intervention will be provided by the lead investigator (SS) who is trained in the delivery of this treatment and has about 10 years of experience in the management of musculoskeletal disorders, including LBP.

In order to develop the pain education resources in Nepali, the first step is the development of curriculum for pain education for patients with LBP^29^ in Nepal. The curriculum was first outlined in English (by SS) in the similar manner recommended by the developers^29^ and was reviewed and approved by both the developers (see online supplementary appendix 1). Based on the curriculum, the pain education materials and patient handouts were created (by SS) in Nepali. The clinical cases and pain stories that were compiled are actual stories collected from patients and clinicians in Nepal but will be anonymously shared to provide reasoning based on contemporary pain biology knowledge.^29^ Pictures that are found in Explain Pain resource materials^29 40 41^ were adapted in the Nepali version.

10.1136/bmjopen-2018-022423.supp1Supplementary file 1

The pain education handout and materials that are produced in Nepali is proofread and will first be pretested in 5–10 Nepalese with LBP as needed, and corrected, if necessary, before using in the feasibility study participants. The final handouts will then be printed for the use in the current study. This adapted process will ensure that the Nepali pain education materials produced are valid and culturally appropriate. However, for the purpose of the full trial, the difficulty in understanding the treatment will be assessed in the current feasibility study, and any modifications required will be made.

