9	Satisfaction of treatment	All the participants in both the conditions will be asked to respond to the Patient Global Assessment of Treatment Satisfaction scale at 1 week following treatment.^65 66^ The question asked will be, ‘*How satisfied are you overall with the study treatment?*’ Responses to this question are made on a five-point categorical scale (0=‘*Very dissatisfied*’; 1=‘*Dissatisfied*’; 2=‘*Neutral or no preference’*; 3= ‘*Satisfied*’; 4=‘*Very satisfied*’).	Mean treatment satisfaction scores will be computed for each treatment condition separately. Between-condition differences will be evaluated using a t-test.
10	Difficulty in understanding the information provided by the physiotherapist.	All the participants will be asked about the difficulty in understanding the information provided by the physiotherapist. The question asked will be, ‘*How difficult was it for you to understand* the *information provided by the physiotherapist?*’ Responses will be provided on a 5-point Likert scale, where 1=‘*Very easy*’, 2=‘*Easy*’, 3=‘*Neither easy nor difficult*’, 4=‘*Difficult*’, 5=‘*Very difficult*’.	The differences in the difficulty in understanding the information provided will be compared between the two groups.
11	Difficulty in understanding the instructions for what to do.	All participants will be asked about the difficulty in understanding the instructions provided by the physiotherapist for what to do at home. The question asked will be, ‘*How difficult was it for you to understand the instructions provided by the physiotherapist for what to do at home?*’ using a on a 5-point Likert scale, where 1=‘Very easy’, 2=‘*Easy*’, 3=‘*Neither easy nor difficult*’, 4=‘*Difficult*’, 5=‘*Very difficult*’.	Frequencies and rates of each response category will be computed for each group separately.
12	Adverse events	All participants will be asked about any adverse events after treatment. All responses will be recorded verbatim.	The number of adverse events listed will be computed for each treatment condition separately. The responses will be analysed qualitatively (see text).

LBP, low back pain.

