Score on the credibility of treatment scale	Control condition is >0.50 SD credible than pain education group.	Develop a new control condition for the EP trial and pilot test to ensure that its credibility rating is <0.50 SD different from pain education group.	-	The credibility scores of the two conditions are within 0.50 SD units of each other.
Adherence to treatment	<50% attend the treatment session after randomisation.	Identify reasons for not attending the treatment session in order to increase attendance in the full trial.	50%–80% of the participants attend the treatment session.	80% or more of the participants attend the treatment sessions.
Difficulty scale	If ≥50% participants in the experimental group rate pain education as very difficult, very easy, easy or neither easy nor difficult.	Make the intervention a little more challenging if more than half of the participants report 1–3 out of 5 in the difficulty scale, by increasing the depth of the education, by adding more pain biology education content. Whereas if more than half participants report the intervention as very difficult, reduce the complexity. Re-evaluate complexity in a second cohort of at least five participants to ensure appropriate level of difficulty.	-	≥50% participants in the experimental group rate pain education as a ‘difficult’ intervention (4 out of 5 in the difficulty scale). This is the preferred difficulty level because we want pain education intervention to be difficult enough to challenge participants but not too easy or very difficult.

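### Within the trial, understanding of the adapted pain education is captured only as self-rated difficulty, so the Table 4 actions cannot tell understood material from material that merely felt easy or challenging

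*Protocol article*

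**What the plan says.** The section Pain education for LBP describes the education as having defined content: "This intervention has a list of target key concepts to be delivered". The section Why the feasibility trial? gives the need for significant cultural adaptation as its first reason. The section Pain education group describes a pretest in 5–10 people, as needed, and then passes a further question to the trial: "the difficulty in understanding the treatment will be assessed in the current feasibility study, and any modifications required will be made".

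Table 2 fixes how that is done. Item 10: "All the participants will be asked about the difficulty in understanding the information provided by the physiotherapist". Item 11: "All participants will be asked about the difficulty in understanding the instructions provided by the physiotherapist for what to do at home". Both use a scale from 1 (very easy) to 5 (very difficult).

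Table 4, in its difficulty row, fixes what follows. The action column reads "Make the intervention a little more challenging if more than half of the participants report 1–3 out of 5 in the difficulty scale", to be done "by increasing the depth of the education, by adding more pain biology education content". If more than half find it very difficult, complexity is reduced. After a change: "Re-evaluate complexity in a second cohort of at least five participants to ensure appropriate level of difficulty". If at least 50% of the pain education group rate 4, the row calls for no modification and no close monitoring.

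**The concern.** A difficulty rating has no right or wrong answer. A participant who missed or reversed a key concept can sincerely report that the session was easy, and one who found it challenging may or may not have grasped it. Table 4 nevertheless uses the rating alone to decide whether to deepen, simplify or keep the material.

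Two errors are possible. If a majority found the session easy without taking in the concepts, the rule adds content where clearer content was needed. If at least half found it difficult and did not follow it, the rule passes the material unchanged.

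The population makes this worth closing off. The protocol deliberately includes people with little or no schooling (Participant screening and recruitment), and the materials are newly adapted. Whatever Table 4 decides here goes forward into the planning of the full trial.

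**Working it through.** There is no sample-size or power figure to reproduce. The 40 participants are the team's own estimate, and the point does not depend on it. The check has two parts.

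**1. Is comprehension measured anywhere?**

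- Table 2: items 10 and 11 are self-ratings. Credibility and satisfaction are opinions about the treatment. No item tests recall or understanding.
- Table 3 and Additional measures: pain catastrophising is measured, but it does not test the key concepts and does not enter the difficulty row of Table 4. No pain-knowledge or teach-back measure is listed.
- Pretest (Pain education group; Patient and public involvement): participants give feedback and comments. No comprehension criterion is stated, and the result does not feed Table 4.
- Control group: the only scored knowledge test is the quiz with an 80% pass mark, and it is for the physiotherapists treating the control arm.
- Table 4 re-check: at least five further people, again on level of difficulty.

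**2. What does the rule respond to?**

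Input from the protocol: 20 in the pain education group (Sample size). Table 4 does not say which of the two items it uses; either is a self-rating. The action column says more than half (11 or more of 20) and the criterion column says at least 50% (10 or more), so both are shown. The criterion column also pools very difficult with ratings 1–3; here only ratings 1–3 count, because they are what leads to added content.

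Let p be the true share who would rate 1–3. The chance that content is added is the binomial upper tail,

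P(X ≥ r) = Σ C(20,k) p^k (1−p)^(20−k), summed from k = r to 20.

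The protocol gives no value for p, so every value below is an assumption.

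| p | r = 11 | r = 10 |
|---|---|---|
| 0.40 | 12.8% | 24.5% |
| 0.50 | 41.2% | 58.8% |
| 0.60 | 75.5% | 87.2% |
| 0.70 | 95.2% | 98.3% |
| 0.80 | 99.7% | 99.9% |

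Comprehension enters only through p. Let q be the share who understood, and e1 and e0 the chances of rating 1–3 among those who did and did not understand. Then p = q·e1 + (1−q)·e0. With r = 11:

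- Rating unrelated to understanding (e1 = e0 = 0.7): p = 0.70 and the chance is 95.2%, whether q is 20%, 40% or 80%.
- Rating partly tracks understanding (e1 = 0.8, e0 = 0.6): at q = 20%, p = 0.16 + 0.48 = 0.64 and the chance is 85.8%; at q = 80%, p = 0.64 + 0.12 = 0.76 and the chance is 99.0%.
- The same gap at a lower level (e1 = 0.7, e0 = 0.5): at q = 20%, p = 0.14 + 0.40 = 0.54 and the chance is 55.6%; at q = 80%, p = 0.56 + 0.10 = 0.66 and the chance is 89.7%.
- Misunderstood material feels easier (e1 = 0.6, e0 = 0.8): at q = 20%, p = 0.12 + 0.64 = 0.76 and the chance is 99.0%; at q = 80%, p = 0.48 + 0.16 = 0.64 and the chance is 85.8%. The rule is then more likely to add content when fewer understood.

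Losses to follow-up change little. At p = 0.70 the chance is 96.0% with 17 assessed (15% lost) and 90.7% with 14 assessed (30% lost).

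The no-change action works the same way. Read p as the share who would rate 4 and use the r = 10 column: at p = 0.60 the material passes unchanged with probability 87.2%, and comprehension does not enter the rule.

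**The case against.** The strongest reply is that the protocol does what it says. The listed objective is difficulty in understanding, and items 10 and 11 measure difficulty. That stands: objective and measure do not contradict each other, and a reader who infers that the trial fails its own stated objective goes too far. What remains is that Table 4 turns the rating into a decision about content, which a rating of ease cannot support by itself.

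Other stronger readings are also unsupported:

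- *Nothing in the plan checks the materials.* The pretest, with patient feedback and correction, does. It lacks a stated comprehension criterion, so it narrows the gap without closing it.
- *One misunderstood message rated easy triggers added content.* The trigger is a majority of the group.
- *The full trial will test material that was not understood.* No passage shows that rated ease and comprehension diverge here. The change called for is small, and a second cohort follows it, although that cohort is again judged on difficulty.
- *Participants are rating the teacher to the teacher.* The interviewer is a physiotherapist blinded to group, and the lead investigator delivers the education.

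A comprehension check has its own costs. It would be unvalidated, it lengthens an interview whose burden is itself under study (Table 4 has a row on the feasibility of outcome assessment), and pain biology answers could reveal the arm to the assessor. The last is largely met by order: if the questions come after all outcome and blinding questions, that participant's data are already recorded.

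**Conclusion.** The point holds in a limited form. Among the trial's own outcomes, understanding is captured only as self-rated difficulty, and the Table 4 actions to add content or make no change depend on that rating alone. The same ratings lead to the same action whatever was understood, and the second cohort repeats the limitation. This follows from Tables 2 and 4 without any assumption.

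The size is unknown. The probabilities above rest on assumed rating shares and show how the rule behaves; they do not show how often it would err. If ratings track comprehension closely, little is lost. This is a worthwhile and inexpensive improvement to one decision rule. It does not call the feasibility design as a whole into question.

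**What to change.** 1. At the end of the 1-week interview, after all outcome and blinding questions, ask 3–5 short spoken questions drawn from the curriculum's key concepts. Ask them in both arms, so that being asked does not reveal allocation.
2. Report the share of the pain education group answering each item correctly. Set the cut-off for understood before recruitment starts. With 20 people each answer moves a share by 1/20 = 5 percentage points, so the cut-off should be read as a guide to revision.
3. In Table 4, allow the add-content and no-change actions only when the cut-off is met. Otherwise revise the material for clarity, whatever the difficulty rating.
4. Use the same questions in the second cohort.
5. While editing that row, reconcile at least 50% with more than half. At exactly 10 of 20 rating 4 and the other 10 elsewhere, the modify and no-change columns are both met.

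Cost: a few minutes of interview time, a small set of unvalidated questions to write and pretest in Nepali, and a wording change in one row of Table 4.
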